## 5.3 Study Treatment

## 5.3.1 Sorafenib Group (sorafenib maintenance therapy)

Sorafenib is started from day +30 until day +180 post-transplantation if patients meet the inclusion criterion on day +30. For patients who do not meet the inclusion criterion on day +30 but who do so within 31-60 days post-transplantation, sorafenib is administrated at 31-60 days post-transplantation and continued until day +180. The initial dose of sorafenib is 400 mg orally BID. In cases of grade 3 or worse AEs, dose modifications including dose reductions or interruptions are allowed at the investigator’s discretion. After the resolution of AEs, the dose is re-escalated from 200 mg QD or 200 mg BID to 400 mg BID at the discretion of the investigator.

## 5.3.2 Control Group (non-maintenance therapy)

Neither sorafenib nor other FLT3 inhibitors can be used unless the patients experience relapse.

## 5.4 Follow-up

Disease assessment including routine blood and BM assessment will be regularly performed post-transplantation. BM assessment, including BM smear and FLT3-ITD mutation is performed before randomization, every month for the first three months after enrollment, every two months from the 4th to 9th month after enrollment, and then every three months until the study is completed.

All subjects will be followed for safety and tolerability within 210 days post-transplantation. With the exception of GVHD and hematologic AEs, all AEs are graded according to CTCAE version 4.0. aGVHD, cGVHD and hematologic AEs are graded as AEs according to our self-defined criteria.

# 6. Efficacy Assessments

## 6.1 Definitions

- - Relapse is defined as reappearance of leukemic blasts in the peripheral blood or ≥ 5% blasts in the BM as pirate or biopsy not attributable to any other cause or reappearance or new appearance of extramedullary leukemia.
- CRc comprises CR, CRp, and CRi.
- CR is defined as BM blasts <5%; absence of circulating blasts and blasts with Auer rods; absence of extramedullary disease; ANC ≥1·0×10^9^/L and PLT ≥100×10^9^/L.
- CRp is defined as all CR criteria except for incomplete platelet recovery (<100×10^9^/L).
- CRi is defined as all CR criteria except for incomplete hematologic recovery with residual neutropenia <1·0×10^9^/L and/ or thrombocytopenia <100×10^9^/L.
  - Partial remission (PR) is defined as 5%-20% blasts with or without extramedullary leukemia.
  - No evidence of response (NR) is defined as a failure to obtain PR or better.

## 6.2 Primary Efficacy Endpoint

- The 1-year cumulative incidence of relapse post-transplantation.

## 6.3 Secondary Efficacy Endpoints

- - OS is defined as the time from transplantation until death from any cause.
- LFS is defined as survival in continuous CR without relapse, and refer to the time from transplantation until relapse or death from any cause.

## 6.4 Schedule and methods of Efficacy Assessments

Disease assessment including routine blood and BM assessment will be regularly performed post-transplantation. Routine blood is monitored before randomization, twice a week for the first month after enrollment, once a week from the 2nd to 3rd month after enrollment, and then once every two weeks until the study is completed. BM assessment, including BM smear and FLT3-ITD mutation is performed before randomization, every month for the first three months after enrollment, every two months from the 4th to 9th month after enrollment, and then every three months until the study is completed. Mutation analysis of the FLT3-ITD (exons 14 and 15) gene is performed by polymerase chain reaction and direct sequencing. All subjects who complete treatment or withdraw from the study must receive efficacy assessment.

# 7. Safety Evaluation

All subjects enrolled in the study will be evaluable for safety and tolerability. Safety and tolerability will be assessed with vital signs, physical examination, clinical symptoms, and clinical laboratory evaluations (hematology, serum chemistry, urinalysis, electrocardiogram, and chest imaging examination). With the exception of GVHD and hematologic AEs, all AEs will be evaluated within 210 days post-transplantation according to CTCAE version 4.0. aGVHD, cGVHD and hematologic AEs are graded as AEs according to our self-defined criteria.

### 7.1 Medical History

Each subject's medical history must be obtained at screening. Information on any prior or existing medical conditions will be recorded on the appropriate CRF.

### 7.2 Vital Signs and Physical Examination

Vital signs and results of physical examination must be documented before randomization, once a week for the first month after enrollment, once every two weeks from the 2nd month after enrollment until 210 days post-transplantation. The next 8 items must be performed:

⚫ Physical examination

⚫ Heart rate

⚫ Blood pressure

⚫ Body temperature

⚫ Rate of respiration

⚫ Body weight

⚫ ECOG performance status

⚫ Signs of infection

### 7.3 Clinical Symptoms

During the study, the patients' clinical symptoms must be documented. The clinical symptoms may be associated with the administration of sorafenib reported previously, [^15^](#_ENREF_15) including rash, hand-foot-skin reaction, dermatitis, erythema, flushing, pruritus, dry skin, alopecia, stomatitis, diarrhea, nausea, vomiting, pancreatitis, weight loss, anorexia, fatigue, fever, headache, sensory neuropathy, myalgia, arthralgia, abdominal pain, cardiac ischaemia, dyspnea, infections, bleeding and hypertension. Besides, some retrospective studies have demonstrated that application of sorafenib post-transplantation might increase the incidence of GVHD.[^16^](#_ENREF_16)^,^ [^17^](#_ENREF_17)

### 7.4 Clinical Laboratory Evaluations

Before initiation of the study, the monitors will document the normal range of each test in every involved laboratory. During the study, the next items must be performed:

⚫ Routine blood: white cell counts, neutrophil cell counts, hemoglobin, and platelet counts

⚫ Hepatic function: total bilirubin (both direct bilirubin and indirect bilirubin must be documented when the total bilirubin elevates), ALT, AST, lactic dehydrogenase, alkaline phosphatase, albumin and total protein

- Renal function: serum creatinine, urea nitrogen and uric acid
- Other biochemical indicators: amylase and lipase
- Electrolytes: sodium, potassium, calcium and magnesium
- Coagulation function: prothrombin time, prothrombin time-international normalized ratio, activated partial thromboplastin time and fibrinogen
- Urinalysis: protein, glucose and erythrocyte
- Electrocardiogram
- Chest imaging examination

## 8 Adverse Events and Serious Adverse Events (SAEs)

The investigator is responsible for detecting, documenting and reporting events that meet the definition of an AE or SAE.

### 8.1. Definitions

## 8.1.1 Adverse Events

An AE is any untoward medical occurrence in a subject of a clinical investigation, which does not necessarily have a causal relationship to the medicinal product. Therefore, an AE can be any unfavorable and unintended sign, including an abnormal laboratory finding, symptom, or disease (new or exacerbated), whether or not it is considered to be related to the product. This definition includes any newly occurring event or previous condition that has increased in severity or frequency since the administration of the product. However, relapse or death due to relapse should not be recorded as AEs.

## 8.1.2 Serious Adverse Events

A serious adverse event is any untoward medical occurrence that, at any dose:

- - Results in death
  - Is life-threatening
  - Requires hospitalization or prolongation of existing hospitalization - ie, the AE requires at least a 24-hour inpatient hospitalization or prolongs a hospitalization beyond the expected length of stay.

Hospitalization or prolongation of existing hospitalization for social reasons will not be reported as an SAE.

- - Results in disability/incapacity
  - Congenital anomaly/ birth defect
  - Important medical event

Medical or scientific judgment should be exercised in deciding whether SAE reporting is appropriate in other situations. An important medical event is an event that may not result in death, be life-threatening, or require hospitalization, but is clearly of major clinical significance. The AE may jeopardize the subject or require intervention to prevent a serious outcome.

## 8.2 Assessment of Severity

With the exception of GVHD and hematologic AEs, all AEs are graded according to CTCAE version 4.0. Considering our inclusion criteria are ANC ≥ 1.0×10^9^/L and PLT ≥ 30×10^9^/L within 60 days post-transplantation, grade 3 hematologic AEs are defined as ANC < 1.0-0.5×10^9^/L or PLT < 30-20×10^9^/L, and grade 4 hematologic AEs as ANC < 0.5×10^9^/L or PLT < 20×10^9^/L. When CTCAE version 4.0 criteria do not apply, severity will be defined according to the following criteria:

| **Severity** | **Description** |
| --- | --- |
| Grade 1- Mild | Asymptomatic or mild symptoms; clinical or diagnostic observations only; intervention not indicated |
| Grade 2- Moderate | Minimal, local or noninvasive intervention indicated; limiting age-appropriate instrumental activities of daily living (ADL) |
| Grade 3- Severe | Medically significant but not immediately life threatening; hospitalization or prolongation of hospitalization indicated; disabling; limiting self-case ADL |
| Grade 4- Life-threatening | Life-threatening consequences; urgent intervention indicated |
| Grade 5- Death | Death |

In this study, aGVHD is graded according to the 1994 Consensus Conference on Acute GVHD Grading,[^18^](#_ENREF_18) and cGVHD is graded according to the National Institutes of Health (NIH) criteria.[^19^](#_ENREF_19) aGVHD and cGVHD are graded as AEs according to the above criteria. Grade I aGVHD without intervention is graded as grade 1 AE, grade I aGVHD with intervention as grade 2 AE, grade II aGVHD as grade 3 AE, grade III-IV aGVHD as grade 4 AE, and death due to aGVHD as grade 5 AE. With regards to cGVHD, mild cGVHD without systematic intervention is graded as grade 1 AE, mild cGVHD with systematic intervention as grade 2 AE, moderate cGVHD as grade 3 AE, severe cGVHD as grade 4 AE, and death due to cGVHD as grade 5 AE.

## 8.3 Assessment of Causality

The investigator must determine the relationship of each AE and SAE to study treatment. Relationship of an AE or SAE to study treatment will be defined according to the following criteria:

- - Definite: There is a clear temporal relationship to study treatment, with no other possible cause.
  - Possible: A temporal relationship to study treatment is not clear, and alternative etiologies are possible.
  - Not related: There is no temporal relationship to study treatment, and/or there is evidence of an alternative cause such as a concurrent medication or illness.

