## 9.2. Premature Termination of the Study

Reasons for premature termination of the study include external events, repetition of SAEs, growing incidence of treatment-related death and slow enrolment in the study. All subjects will be informed of premature termination of the study by written consents. Any subjects who decide to discontinue participating in the study must report to the principal investigator.

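### The three causality categories in Protocol section 8.3 leave gaps, overlap and rank stronger timing below weaker timing, so attribution to sorafenib is unreliable and likely biased downward

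*Protocol*

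**What the plan says.** Section 8.3 makes attribution compulsory and puts it in the investigator's hands: "The investigator must determine the relationship of each AE and SAE to study treatment". It then defines three categories as the criteria to be applied.

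- The strongest category, Definite, demands clear timing and rules out every other candidate cause.
- The middle category is worded as follows: "Possible: A temporal relationship to study treatment is not clear, and alternative etiologies are possible".
- The weakest category, Not related, covers events whose timing shows no link to treatment. Its wording then widens it: "and/or there is evidence of an alternative cause such as a concurrent medication or illness".

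Section 8.4 makes the investigator's view of relatedness a required item on the SAE form, which goes to the ethics committee within 24 hours. Section 9.2 lists "growing incidence of treatment-related death" among the reasons for ending the study early. It gives no definition of the term, no threshold and no reference to 8.3. Section 7.3 lists symptoms that may be associated with sorafenib, among them rash, diarrhea, infections and bleeding, and adds that "application of sorafenib post-transplantation might increase the incidence of GVHD".

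**The concern.** A causality scale should place every event in exactly one category, and better evidence of timing should never lower the attribution. The wording of 8.3 fails on both counts. Possible is tied to unclear timing, and under Not related evidence of another cause is enough on its own. An event that follows dosing closely but has a competing explanation is therefore kept out of both related categories.

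This matters in a transplant population. Sorafenib starts between day +30 and day +60, when other illness and other drugs offer ready explanations for the symptoms that section 7.3 associates with sorafenib. GVHD is both a suspected drug effect and a complication of the transplant itself. At stake are the relatedness field on every SAE form, the relatedness recorded for every AE, consistency across seven centers in an open-label trial, and possibly one stated reason for stopping the study.

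**Working it through.** No figure in the Protocol needs reproducing; the check is one of logic.

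**Inputs, all from section 8.3.**

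- Definite = clear temporal link AND no other possible cause.
- Possible = temporal link not clear AND alternative causes possible.
- Not related = no temporal link OR evidence of an alternative cause (the text joins these with 'and/or').

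The text separates an alternative that is merely possible from one for which there is evidence, so the alternative cause needs three levels. Timing also has three: clear, unclear, none. That gives 3 × 3 = 9 combinations.

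| Temporal link | No alternative | Conceivable, no evidence | Evidence of alternative |
| --- | --- | --- | --- |
| Clear | Definite | **no category** | Not related |
| Unclear | **no category** | Possible | **Possible and Not related** |
| None | Not related | Not related | Not related |

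**Result.** 6 of 9 combinations fall in exactly one category, 2 of 9 in none and 1 of 9 in two (6 + 2 + 1 = 9).

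**Ordering.** In the middle column the alternative cause is held constant at conceivable. Unclear timing gives Possible, while clear timing gives nothing. In the right-hand column, unclear timing still allows Possible, while clear timing allows only Not related. In both columns, stronger timing removes the only related category available.

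**A stricter reading of 'evidence'.** It could be taken to mean evidence that the other cause actually produced the event, rather than evidence that another candidate cause was present. Fewer clear-link events would then become Not related, but those events would move to the empty cell in the middle column. Neither reading takes them to Possible.

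**Where the attribution is used.**

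- Section 8.4: all AEs and SAEs are recorded and every SAE is reported, whatever the attribution. Relatedness is one field on the SAE form.
- Section 11.3.2.3: safety is assessed by incidence and severity and by changes from baseline. No analysis by relatedness is stated.
- Section 5.3.1: dose modification is triggered by grade.
- Section 11.3.2.2: the competing event is non-relapse mortality, which needs no causality judgement.
- Section 9.2: treatment-related death is a termination reason, not linked to any definition.

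The defect therefore reaches the attribution itself and, by inference only, section 9.2.

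**The case against.** The strongest reply is that little depends on the label. Every AE and SAE is recorded and every SAE is reported regardless of attribution. The stated analysis is by incidence and severity in all randomized subjects, so excess toxicity can be seen against a concurrent untreated control arm without any causality judgement. Dose changes follow grade. Section 9.2 also lists repeated SAEs, which need no attribution. Section 7.3 alerts investigators to sorafenib's possible part in GVHD, rash and diarrhea, and eligibility excludes active acute GVHD, uncontrolled infection and major organ dysfunction. All of this stands, and it limits the consequence. It does not repair the wording of a rule that investigators must apply to every event.

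Three stronger readings are tempting, and the document does not support them.

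- A reader might infer that any clear-link event with another conceivable cause is coded Not related. Section 8.3 asks for evidence of the alternative; without it the event simply has no category.
- A reader might infer that the safety signal is suppressed or that toxicity is under-counted. Only the attribution is exposed. The planned counts do not filter on it.
- A reader might infer that clear timing with a competing cause is the dominant combination, or that treatment-related deaths are necessarily under-counted. The Protocol gives no frequency for the first. For the second, 9.2 neither defines the term nor cites 8.3.

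**Conclusion.** The point holds for attribution only. As written, the categories are not exhaustive (2 of 9 combinations unplaced), not mutually exclusive (1 of 9 placed twice) and wrongly ordered with respect to timing. Attribution to sorafenib will be inconsistent. It is likely biased downward, because clear-link events with a competing cause cannot reach a related category. The direction rests on the literal wording and on the expectation that competing causes are common after transplant, which is reasonable but not quantified in the Protocol. The size cannot be computed.

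Any effect on a count of treatment-related deaths is conditional on that count using 8.3, the only place where the Protocol defines relatedness. The primary efficacy analysis, total AE counts, SAE reporting and the incidence and severity analysis are unaffected. The correction should be made: it concerns safety attribution and, plausibly, a termination reason, and it is cheap.

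**What to change.** Rewrite the three definitions in section 8.3 so that each event has exactly one place:

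- **Definite:** clear temporal link and no other possible cause.
- **Not related:** no plausible temporal link, or an alternative cause that fully explains the event.
- **Possible:** every other event, including a clear temporal link with an alternative cause that does not fully explain it.

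Possible is then the residual category, so nothing is left out. Definite and Not related cannot overlap, because Definite requires a clear link and no other possible cause. In the table above, both empty cells become Possible. The two evidence cells with a clear or unclear link become Possible, unless the alternative fully explains the event.

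In section 9.2, state that treatment-related means Definite or Possible under 8.3. Carry the wording into the CRF guidance and review attributions already made under the present text.

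The cost is one paragraph in 8.3, one sentence in 9.2, matching CRF guidance and a review of existing attributions, some of which may change. The downside is that more events will be labelled possibly related.

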## 8.4 Recording and Reporting AEs and SAEs

All AEs and SAEs must be recorded in the appropriate CRF, whether or not they are associated to be causally related to study treatment. Each SAE must be reported promptly on the Serious Adverse Event Report Form, and submitted to the Independent Ethics Committee within 24 hours by the investigator. The information recorded on the Serious Adverse Event Report Form will include at least the following: subject number, identity of the event, study drug name and dose, investigator's assessment of the event's severity and relationship to study treatment, and investigator's name and signature. Clinical monitors must collect and verify detailed information of AEs and SAEs when examining original medical records. All AEs and SAEs should be followed up until resolved.

# 9. Rules of Withdrawal

## 9.1. Subjects Withdraw from the Study

Subjects can withdraw from the study at any time for any reason without impact on the investigator’s right to treat disease for subjects. Based upon the interest of subjects, the investigator has the right to request subjects to withdraw from the study for any reason including concomitant disease, AEs or treatment failure. The core group of clinical study reserves the right to request subjects to withdraw from the study for deviation(s) from the protocol, administrative reasons, or other effective or ethical reasons.

The last assessment for subjects must be performed and documented in the CRF regardless of the time and reason for withdrawal. The reason for withdrawal from study participation must be documented in the CRF. All documents related to subjects should be completed. Despite withdrawal from the study, those subjects should be followed up and documented about their diseases until withdrawal of informed consents.

For subjects who withdraw from the study due to concomitant diseases or AEs, the details must be documented in the CRF with other appropriate and valuable data attached.

## 9.2. Premature Termination of the Study

Reasons for premature termination of the study include external events, repetition of SAEs, growing incidence of treatment-related death and slow enrolment in the study. All subjects will be informed of premature termination of the study by written consents. Any subjects who decide to discontinue participating in the study must report to the principal investigator.

# 10. Rules of Follow-Up

## 10.1 Follow-up Period

Starting from randomization.

## 10.2 Visit Scheduling

Every week for the first three months after enrollment, and then every month until the study is completed.

## 10. 3 Contents

The contents of every follow-up visit include complaints of subjects, vital signs, physical examination, clinical symptoms and clinical laboratory evaluations (hematology, serum chemistry, urinalysis, electrocardiogram, chest imaging examination, and BM assessment). All of the results must be documented in the original medical record.

# 11. Data Analysis and Statistical Considerations

## 11.1. Hypotheses

The primary endpoint is the 1-year cumulative incidence of relapse post-transplantation. The null and alternative hypotheses are designed with the goal of demonstrating the superiority of sorafenib maintenance over non-maintenance post-transplantation with respect to relapse. Superiority will be determined using the following hypothesis:

H0: incidence of relapse with sorafenib maintenance ≥ incidence of relapse with non-maintenance post-transplantation

H1: incidence of relapse with sorafenib maintenance < incidence of relapse with non-maintenance post-transplantation

## 11.2 Study Design Considerations

This prospective, open-label, multicenter, randomized, phase 3 study compares the efficacy of sorafenib maintenance and non-maintenance post-transplantation in FLT3-ITD AML undergoing allo-HSCT. The primary outcome is the 1-year cumulative incidence of relapse post-transplantation, and the study is designed to determine if sorafenib maintenance is superior to non-maintenance post-transplantation in the study population with respect to relapse. Base on the reported 1-year cumulative incidence of relapse of 40% for non-maintenance post-transplantation in FLT3-ITD AML undergoing allo-HSCT,[^20^](#_ENREF_20) a clinically meaningful reduction in 1-year cumulative incidence of relapse would be 20% for sorafenib maintenance post-transplantation.

